### Power Calculation

Functional endpoint: For the sample size calculation, the results of the FLOWER-MI trial will be used. In this study, which enrolled multivessel disease patients with at least one non-culprit lesion >50%, PCI was performed in 388 of 586 patients (66.2%) in the FFR-guided group and in 560 of 577 patients (97.1%) in the angiography-guided group; 366 of 826 (44.3%) lesions in the FFR group were reclassified from angiographically significant to non-significant based on FFR. Of note, although we allow patients with lesions >30% in our study, we foresee that [based on the results of the FLOWER-MI (10)], about 97% of the participants in our study will have at least one lesion >50%. Conservatively, we hypothesize a rate of decision to not perform PCI in our angiography group 4 times higher than that observed in the FLOWER-MI study (i.e., 13%). In the QFR group, we hypothesize a conservative decision in 33% (similar to that observed in the FLOWER-MI study). Based on this hypothesis, 176 patients are required to have a 90% chance of detecting, as significant at the 5% level, a decrease in the primary outcome measure from 33% in the QFR group to 13% in the angiography group.

Clinical endpoint: The clinical endpoint combines hard endpoints and angina: in the FORZA trial, comparing a FFR-guided with a OCT-guided PCI strategy, a composite of MACE + significant angina (all-cause death, non-fatal myocardial infarction, target vessel revascularization, SAQ <90) was taken. The incidence of this endpoint was 14.8% at 1 year in the FFR group (23). The incidence of the same endpoint in the FAME trial was 32.4% at 1 year in the angiography group (3). Given these assumptions, 176 patients are required for a power of 80% and an alpha error of 5% to observe a difference assuming an incidence of 14.8% in the QFR group and 32.4% in the angiography group.

With regards to the change in SAQ, this endpoint was also used in a number of studies, including the ISCHEMIA trial (24): In the TARGET FFR study (25), 260 patients received first angiographically guided PCI and were then randomized (1:1) to a physiology-guided incremental optimization strategy or a blinded coronary physiology assessment. SAQ was a secondary endpoint in this study. A direct comparison with our protocol is impossible (all patients received PCI in TARGET FFR, while our hypothesis is that QFR will prevent futile PCIs and increase necessary ones), however the change in SAQ summary score at three months in both groups was in the range of 21 ± 25. Patients with a larger FFR change had a higher 3-months SAQ (86 ± 24 vs. 72 ± 30, *P* = 0.02 with *n* = 47 and 52 per group). If a similar difference were to be observed in our study, 144 patients would be required with a 90% 1-beta and a 5% alpha. In the FORZA study (23), the SAQ similarly improved from ~82 to ~98 (data reported only in online Figure 1). If we assume a SAQ of 98 in the QFR group and 86 in the reference group, with a SD of 21, 130 patients would be necessary.

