#### SAQ Questionnaires

The first SAQ questionnaire will be administered before the staged revascularization, i.e., ~4 weeks after the ACS event. The SAQ-7 provides a quantitative analysis of 5 domains (physical limitation, angina stability, frequency, treatment satisfaction, and quality of life) reflecting the impact of angina on patients' health status during the previous 4 weeks. Scores for each domain go from 0 to 100, with 100 defining absence of limitations. The SAQ score at 1 month after ACS correlates with the subsequent incidence of mortality, hospitalization, and resource use (22). The SAQ-7, along with clinical follow-up data (death, re-hospitalization, re-intervention) will be collected at 3 and 12 months after protocol-mandated complete revascularization during office or telephone visits.

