**Figure 1 F1:**
[figure not shown]
Study procedures.

In another paper of the Glasgow group (26), the authors enrolled 104 patients with angina with 1:1 randomization to PCI or OMT. The primary outcome was angina status at 3 months using the Seattle Angina Questionnaire (SAQ). After 3 months of follow-up, compared with patients treated with OMT only, patients treated by PCI and OMT had greater improvements in SAQ angina frequency (21 ± 28 vs. 10 ± 23; *p* = 0.026). So also in this case the observed improvements in SAQ appear to be larger than those conservatively predicted in our protocol.

Given the above data, we can safely conclude that our sample size of ~200 will allow testing the hypothesis of a difference in SAQ between groups.

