### Hypothesis

A = Change in the SAQSS after 3 months to baseline with QFR-guided treatment

B = Change in the SAQSS after 3 months to baseline with reference treatment

Hypotheses: H0: A = B; H1: A ≠ B (Overall type I error rate = 5% (two-sided) with a power = 90%).

Based on these assumptions, the sample size is 178. We plan to recruit 100 patients per group.

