### Statistical Analysis of Primary and Secondary Endpoints

Data will be presented as counts (percentages) and mean ± SEM as appropriate and will be analyzed using parametric or non-parametric tests. The primary functional endpoint will be assessed as difference in proportions and the relative risk between groups will be estimated with exact 95% confidence intervals and *P*-values. The proportion of patients with primary functional clinical endpoint and other binary outcomes will be analyzed using the same methods, and time to events within 12 months will be compared between groups using log-rank tests. A multivariable stepwise linear regression (*p* < 0.2 to enter, *p* < 0.1 to stay) analysis will be used. Covariates will include age, sex, diabetes, smoking, renal function, previous myocardial infarction, type of acute coronary syndrome presentation, body mass index, vessel(s) involved. The grouping factor (QFR vs. angiography) will be forced into the model. A *p*-value <0.05 (2-sided) will be considered statistically significant. All secondary endpoints will be analyzed by descriptive statistics and appropriate exploratory *p*-values.

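### The SAQ sample-size figures do not follow from their stated inputs: 144 should be 160, 178 has no stated basis, and the reassurance drawn from the PCI-versus-medical-therapy study is not supported

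*Protocol article*

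**What the plan says.** The SAQ material runs from the third part of Power Calculation, through the text after Figure 1, to the Hypothesis section.

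- **First scenario.** In a trial of physiology-guided PCI optimisation, patients with a larger FFR change scored 86 ± 24 at 3 months, against 72 ± 30 in the others. For a difference of this kind, "144 patients would be required with a 90% 1-beta and a 5% alpha". The same paragraph puts the change in summary score in both randomised groups at about 21 ± 25.
- **Second scenario.** "If we assume a SAQ of 98 in the QFR group and 86 in the reference group, with a SD of 21", the article says 130 patients are needed. The SAQ Questionnaires section states: "Scores for each domain go from 0 to 100".
- **Third source.** A randomised study of PCI versus medical therapy reported gains in angina frequency of 21 ± 28 and 10 ± 23. The article comments that "the observed improvements in SAQ appear to be larger than those conservatively predicted in our protocol", and ends: "we can safely conclude that our sample size of ~200 will allow testing the hypothesis of a difference in SAQ between groups".
- **Hypothesis section.** For the 3-month change in the SAQ summary score it sets "Overall type I error rate = 5% (two-sided) with a power = 90" (per cent), then: "Based on these assumptions, the sample size is 178". The plan is to recruit 100 per group.

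**The concern.** Each figure is presented as the result of inputs printed beside it, so each can be checked, and several do not check. The Hypothesis section is the only place where the article writes out a formal null and alternative, and it attaches 90% power to a number whose difference and SD it does not give. A reader who takes the block at face value will believe that about 200 patients give at least 90% power for any SAQ difference the cited literature makes plausible. One of the three cited sources, used as reassurance, implies less than that. The accuracy of the power statement is at stake, and with it how a neutral SAQ result would be read. Enrolment is not at stake.

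**Working it through.** **Inputs.** 1:1 allocation (Consent and Randomization); two-sided 5% (Hypothesis; Statistical Analysis); 90% power; means and SDs as above. The multiplier is (1.960 + 1.2816)² = 10.507 for 90% power.

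**Formulas.** Patients per arm = 10.507 × (SD₁² + SD₂²) / difference². Power = Φ(difference / √((SD₁² + SD₂²)/n) − 1.96), with n per arm.

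**1. The 144.**
- 10.507 × (24² + 30²) / 14² = 10.507 × 1476 / 196 = 79.1, so 80 per arm and 160 in total. The t-test solution is 162.
- At 72 per arm: 14 / √(1476/72) = 3.09, and 3.09 − 1.96 = 1.13, so power is 87%.
- 144 is not recovered at two-sided 5% and 90% power with both stated SDs. Optimal unequal allocation still needs 157. A common SD of 25.9 would give 144, but it is not stated. The nearest match is SD 30 at 80% power (146), which contradicts the stated 90%.

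**2. The 130.**
- 10.507 × 2 × 21² / 12² = 64.4, so 65 per arm and 130. The article's figure reproduces.
- For a score confined to 0–100 with mean m, the SD cannot exceed √(m(100 − m)). At m = 98 this is √(98 × 2) = 14.0 (14.1 as a sample SD with 65 patients). This takes the SAQ score in the scenario to share the 0–100 range stated for its domains.
- An SD of 21 therefore cannot hold in the QFR arm. It could hold only as a root-mean-square over both arms, for example 14 and √(2 × 441 − 196) = 26.2.
- A smaller SD would lower the required number, so this error does not understate it.

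**3. The reassurance from the third source.**
- Between-group difference: 21 − 10 = 11 points, against 14 and 12 above. Standardised: 11/25.6 = 0.43, against 14/27.2 = 0.52 and 12/21 = 0.57.
- 10.507 × (28² + 23²) / 11² = 10.507 × 1313 / 121 = 114.02, so 115 per arm and 230.
- Power at 89 per arm: 11 / √(1313/89) = 2.86, giving 82%. At 100 per arm: 11 / √(1313/100) = 3.04, giving 86%.
- The figure concerns angina frequency only; the hypothesis concerns the summary score.

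**4. The 178.**
- At 90% power, 89 per arm implies a standardised difference of 3.2415 × √(2/89) = 0.486, which is not stated anywhere.

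| Difference / SD from the article | Total at 90% power |
|---|---|
| 12 / 21 | 130 |
| 14 / 25 | 136 |
| 14 / 27.2 (SDs 24 and 30) | 160 |
| 12 / 25 | 184 |
| 11 / 25.6 (SDs 28 and 23) | 230 |

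- None gives 178. 160 / 0.90 = 178, but no dropout rate is stated, and the article's own figure for that scenario is 144, not 160.

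**5. What the planned size can detect.** With the article's SD of change (25) and 100 evaluable patients per arm: 3.2415 × 25 × √(2/100) = 11.5 points at 90% power, and 2.8016 × 25 × √(2/100) = 9.9 points at 80%. With an assumed 90 per arm: 12.1 and 10.4 points.

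**The case against.** The strongest reply is that little depends on this block. Both primary endpoints are sized at 176, which supports about 200 without any SAQ argument. The SAQ summary-score change is listed as secondary, and secondary endpoints get descriptive statistics and exploratory p-values. Two hundred patients give about 95% power for a true 14-point difference (SDs 24 and 30). All of this stands, and it limits the severity.

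Three narrower replies stand in part:
- **The 178.** The pair 12/25 gives 184, which is close, and a full protocol may state a dropout rate that the article omits. So it is fair to ask for the inputs. It does not follow that no derivation exists. But the article prints 178 as following from what it has just stated, and it does not.
- **The larger-than-predicted remark.** The article never defines the predicted improvement. Read as a gain within one arm, 21 exceeds the gain of about 16 (82 to 98) quoted from the FFR-versus-OCT trial. Power for a group comparison depends on the difference between arms, however, and there the remark is unsupported.
- **Comparability.** The article itself says that a direct comparison with the PCI-optimisation trial is impossible, so the weakness of the 14-point figure as a forecast is partly acknowledged.

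A reader might go further and infer that the trial has almost no power for SAQ, by shrinking the 11 points in proportion to the assumed difference in PCI use (67% under QFR, 87% under angiography) or to the 44.3% reclassification rate. The documents do not support this. The QFR arm is assumed to receive less PCI, so scaling a benefit of PCI over medical therapy would favour angiography, the reverse of the hypothesis. A net difference in PCI use does not count how many patients change treatment, since the article expects QFR both to prevent some procedures and to add others. The 44.3% counts lesions, not patients. And the 11 points belong to one SAQ domain.

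**Conclusion.** The SAQ block is wrong as written in specific, checkable places. The 144 should be 160 (162 by t-test). The SD of 21 is impossible in an arm with mean 98 unless it is an average over both arms. The 178 is not produced by any stated difference and SD at 90% power. The claim that about 200 patients safely suffice does not hold at 90% power for the 11-point difference cited in its support (86% at 200, 82% at 178).

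These results assume equal allocation, two-sided 5%, the article's own SDs and complete SAQ data. They do not show that the trial is too small: its size is carried by the primary endpoints, and the SAQ change is exploratory. This is a reporting correction and does not make the design unsound.

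**What to change.** - Correct 144 to 160 (or 162, naming the t-test).
- Remove the 98 versus 86 with SD 21 scenario, or re-base it on SDs that are possible on the scale.
- State the difference, SD and any dropout rate behind 178, or withdraw it together with its 90% power claim.
- Replace the larger-than-predicted and safe-conclusion sentences with one statement for the 3-month SAQ summary-score change as a secondary, exploratory endpoint: assuming SD 25, 100 evaluable patients per arm detect 11.5 points with 90% power or 9.9 points with 80%. Add that the detectable difference grows if SAQ data are missing, for example 12.1 and 10.4 points with an assumed 90 per arm. This matters because missing SAQ values are not imputed for the primary analysis.

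The cost is a text change and a less favourable power statement. Enrolment, procedures and endpoints are unchanged.

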**Figure 1 F1:**
[figure not shown]
Study procedures.

In another paper of the Glasgow group (26), the authors enrolled 104 patients with angina with 1:1 randomization to PCI or OMT. The primary outcome was angina status at 3 months using the Seattle Angina Questionnaire (SAQ). After 3 months of follow-up, compared with patients treated with OMT only, patients treated by PCI and OMT had greater improvements in SAQ angina frequency (21 ± 28 vs. 10 ± 23; *p* = 0.026). So also in this case the observed improvements in SAQ appear to be larger than those conservatively predicted in our protocol.

Given the above data, we can safely conclude that our sample size of ~200 will allow testing the hypothesis of a difference in SAQ between groups.

### Hypothesis

A = Change in the SAQSS after 3 months to baseline with QFR-guided treatment

B = Change in the SAQSS after 3 months to baseline with reference treatment

Hypotheses: H0: A = B; H1: A ≠ B (Overall type I error rate = 5% (two-sided) with a power = 90%).

Based on these assumptions, the sample size is 178. We plan to recruit 100 patients per group.

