### Study Endpoints

*Primary endpoint (functional): the primary endpoint (functional) is* the proportion of patients assigned to medical treatment in the two groups (QFR vs. Reference) (see Table 2).

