**Table 2 T2:**
[figure not shown]
Study endpoints.

*Primary endpoint (clinical):* the primary endpoint (clinical) is a composite of patient-oriented events and significant angina (all-cause death, non-fatal myocardial infarction including type 1, 2, 4, unplanned hospitalization for angina or heart failure, unplanned revascularization, SAQ <90) at 12 months.

*Secondary endpoints:* the secondary endpoints include the following (at 3 and 12 months):

– the percentage of discordant results between functional (QFR ≤ 0.80) and angiographic coronary stenosis severity (diameter stenosis >70%).– the change in severity of angina pectoris as assessed by the SAQ summary score.– changes in the SAQ-7 domains (SAQ Physical limitation scale; SAQ angina stability scale; SAQ angina frequency scale; SAQ quality of life; SAQ Treatment Satisfaction).– incidence of a patient-oriented composite endpoint and its components (cardiovascular death, non-fatal myocardial infarction including peri-procedural, unplanned revascularization, unplanned hospitalization for angina, SAQ summary score <90) and its individual components.

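### The only formal null and alternative hypotheses, with the overall 5% error and N=178, are written for a secondary, exploratory endpoint, and the 178 cannot be derived from anything stated

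*Protocol article*

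**What the plan says.** Study Endpoints names two primary endpoints. The functional one is "the proportion of patients assigned to medical treatment in the two groups (QFR vs. Reference"). The clinical one is a 12-month composite of clinical events and SAQ below 90. Among the secondary endpoints, at 3 and 12 months, is "the change in severity of angina pectoris as assessed by the SAQ summary score". The section on statistical analysis of primary and secondary endpoints adds: "All secondary endpoints will be analyzed by descriptive statistics and appropriate exploratory *p*-values".

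The Hypothesis section mentions neither primary endpoint. It sets "A = Change in the SAQSS after 3 months to baseline with QFR-guided treatment" against the same change under reference treatment, and continues: "Hypotheses: H0: A = B; H1: A ≠ B (Overall type I error rate = 5% (two-sided) with a power = 90" per cent. It closes with "Based on these assumptions, the sample size is 178. We plan to recruit 100 patients per group".

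Elsewhere, Power Calculation gives each primary endpoint assumed rates, a 5% alpha, a power and a requirement of 176 patients. Study Design states a superiority expectation in words: fewer events and less angina with QFR guidance.

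**The concern.** One variable carries the overall type I error in one section and is exploratory in another. Both cannot stand. The section that should fix the confirmatory question points to a different variable (SAQ summary score) and a different time (3 months) from the endpoints labelled primary. It also sits badly with the Statistics section, which defines the primary analysis population by a 12-month assessment, and with the Discussion, which places the primary endpoint at 12 months.

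If the primary endpoints were negative and 3-month SAQ change positive, the Hypothesis section could be cited as the prespecified test. In the opposite case, Study Endpoints and Power Calculation could be cited. A hypothesis section exists to rule out that choice. The sample size stated there also has no visible source, so a reader cannot check what effect the SAQ hypothesis was meant to detect.

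**Working it through.** **1. The plan's own figures for the primary endpoints (Power Calculation).** Unpooled two-proportion formula, two-sided 5%, 1:1: n per arm = (z_α + z_β)² × [p₁(1−p₁) + p₂(1−p₂)] / (p₁−p₂)².

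- Functional, 33% vs 13%, 90% power: (1.960 + 1.2816)² = 10.507; 10.507 × 0.3342 / 0.0400 = 87.8, so 88 per arm, **176 in total**. The plan says 176.
- Clinical, 14.8% vs 32.4%, 80% power: (1.960 + 0.8416)² = 7.849; 7.849 × 0.3451 / 0.03098 = 87.4, so 88 per arm, **176 in total**. The plan says 176.

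Both reproduce. The pooled-variance formula gives 182 for each.

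**2. Power for the primaries at 200 evaluable patients** (100 per arm, pooled variance under the null): power = Φ{[√n·|p₁−p₂| − 1.960·√(2p̄(1−p̄))] / √[p₁(1−p₁) + p₂(1−p₂)]}.

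- Functional: (2.000 − 1.166)/0.578 = 1.44, power **92.5%**.
- Clinical: (1.760 − 1.177)/0.587 = 0.99, power **84.0%**.

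**3. The 178 in the Hypothesis section.** That section gives no difference and no SD. For two means, n per arm = 2(z_α + z_β)²/d². With 89 per arm at 90% power, d = √(2 × 10.507/89) = **0.486**. This is 10.2 points at SD 21, 12.1 at SD 25 or 13.1 at SD 27.

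**4. SAQ inputs that the document does state, all at 90% power and two-sided 5%.**

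| Source within Power Calculation | Difference, SD | d | N recomputed | N stated |
|---|---|---|---|---|
| Physiology-guided optimisation study, 3-month scores 86 ± 24 vs 72 ± 30 | 14, √[(24² + 30²)/2] = 27.2 (or 27) | 0.515 (0.519) | 160 (158) | 144 |
| Assumed scores 98 vs 86 | 12, 21 | 0.571 | 130 | 130 |
| PCI vs medical therapy study, angina frequency, 21 ± 28 vs 10 ± 23 | 11, √[(28² + 23²)/2] = 25.6 | 0.43 | 230 | none |
| Cross-combination: 12 points with the SD of 25 quoted for SAQ summary score change | 12, 25 | 0.48 | 184 | none |

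No row gives 178. The third row concerns one SAQ domain, not the summary score, and the document computes no sample size from it. The fourth is a combination that the document does not make; it comes nearest.

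**5. The sections side by side.**

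| Item | Hypothesis | Study Endpoints and analysis section |
|---|---|---|
| Variable | SAQ summary score change | Medical treatment assignment; composite |
| Time | 3 months | 12 months for the composite |
| Status of SAQ change | Carries the overall 5% error and 90% power | Secondary, exploratory p-value |
| N | 178 | 176 and 176 (from Power Calculation) |

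**The case against.** The strongest reply is that the primary endpoints are far from undefined. A reader might infer from the Hypothesis section that neither has a hypothesis at all. The document does not support that. Power Calculation uses the language of hypothesis for the functional endpoint and gives rates, alpha, power and N for both; Study Design states the superiority expectation; and the analysis section names a comparison of proportions at two-sided 0.05. What is missing is a formal statement of these hypotheses and their link to the overall error rate.

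A reader might also infer that the trial's final size rests on 178. It does not: the 176 for each primary endpoint is independently reproducible, and 200 exceeds both.

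Nor do the three variables have equal standing. The endpoint labels are explicit, and the exploratory status of secondary endpoints, followed as written, bars a confirmatory claim on SAQ change. The 178 is also only about 1% above 176, and close to the 184 from a plausible pairing of stated inputs, so it is undocumented rather than implausible.

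All of that stands. It limits the consequence but does not remove the contradiction. The Hypothesis section is also not an isolated slip: the sample-size argument before it ends by concluding that about 200 patients suffice to test a between-group SAQ difference.

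**Conclusion.** The point holds in this form: the only formal hypotheses, with the overall two-sided 5% error, 90% power and N=178, belong to an endpoint that the same document makes secondary and exploratory, while the primaries have only planning assumptions and a verbal hypothesis. The 178 matches no stated difference and SD (implied d = 0.486; stated sizes for SAQ are 144 and 130, and their inputs recompute to about 158–160 and 130).

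The harm is ambiguity about which result is confirmatory, not a shortage of patients. The 92.5% and 84.0% power figures assume 200 evaluable patients, the rates stated in the plan, and each endpoint tested on its own at two-sided 5%.

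**What to change.** Rewrite the Hypothesis section so that:

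- the formal null and alternative hypotheses are (1) equal proportions assigned to medical treatment and (2) equal 12-month composite proportions, in the QFR and angiography groups, and the overall 5% error refers to these;
- the sample-size basis cited is the existing one (176 for each), with power of about 92.5% and 84% at 200 evaluable patients;
- 3-month SAQ summary score change is labelled a secondary, exploratory hypothesis, in line with the analysis section, and not given a place in a confirmatory testing order, which this document does not have;
- 178 is deleted, or the difference and SD that produce it are given.

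The rewrite should also say how the overall 5% covers two primary endpoints, since restating the hypotheses does not settle that by itself.

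The cost is protocol wording only. The planning inputs and the recruitment target of 200 stay as they are. The change should be made and dated before anyone sees outcome data by group.
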